Participants will be sent SMS messages every 3 days as a reminder to measure their BP with the Bluetooth-enabled A&D UA-767 Plus BP monitor (A&D Medical, San Jose, CA). They will be instructed to measure their BP in the morning and evening every third day by using our resting BP protocol (described under Clinic Resting Blood Pressure). They will also receive a tailored positive reinforcement SMS message the day after successful completion of their BP measurements. An app will be installed on their smartphone, which will securely receive and transmit the BP data to the MUSC-housed server. The app will also provide text instructions throughout the BP protocol and a video clip module demonstrating use of the app and the BP monitor.

A weekly SMASK dashboard summary report, tailored to the treating physician’s preferences, will be delivered via email (Figure 3). The report will summarize each subject’s medication adherence and adherence to the BP self-monitoring schedule for the prior 2 weeks. Color coding will be used to indicate where the subject lies relative to the desired goals (ie, SBP <130 mm Hg and adherence score >0.90). In addition, a breakdown of the BP readings obtained over the 2 weeks will be provided with systolic and diastolic pressures. The treating physician will make adjustments to the medical regimen, as indicated and guided by the KDIGO guidelines [49]. The physician will notify the study coordinator of the changes via email. Any medication changes made by the treating physician will be mirrored in the programming of the medication tray after the study coordinator confirms with the patient that the changes have been enacted. The research manager and staff will be contacted via email, and the SMASK participants will be contacted via their preferred mode (SMS, email, or phone) when they fail to measure BP or when the measured BP is outside of the threshold ranges established by the treating physician, or they will be contacted via an SMS text when the SimpleMed+ tray identifies lack of medication adherence.

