### Mobile Health Intervention

The participants randomized to the intervention arm will receive the SMASK mHealth system, described in detail above, for the 6-month active trial. Subjects will be provided and instructed on use of the previously validated A&D BP device, and the SMASK app will be installed on their smartphone. The escalating reminder functions of the SimpleMed+ will be enabled. The SMASK subjects will again receive written and oral instructions on adherence criteria (ie, all medications are to be taken within a 180-min window centered on the dosing time; BP is to be measured every 3 days).

SMASK subjects will complete a questionnaire on beliefs, values, and life goals with the responses used in a tree-structured algorithm to generate tailored motivational and positive reinforcement messages that are delivered to promote self-efficacy for medication adherence and autonomous regulation for sustained behavior change.

A technical support phone number will be provided in several forms (paper copy, refrigerator magnet, and SMASK app) for assistance. At the conclusion of the study, subjects will return the SimpleMed+, A&D BP monitor, and smartphone (if one was borrowed) and complete a brief questionnaire assessing their opinions of the mHealth system.

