**Adverse events**							
	Medication Side Effects Scale [63,64]	✓	✓	✓	✓	✓	✓
	Hypertension/immunosuppression knowledge [59,65] (α=0.70, high-low correlation: *P*<.01)	✓					
	Short Form-8 (α=0.87)	✓	✓	✓	✓	✓	✓
	Perceived Stress Scale (α=0.84-0.86; 2-day test-retest *r*=0.85) [64]	✓	✓	✓	✓	✓	✓

^a^BP: blood pressure.

^b^SBP: systolic blood pressure.

^c^KDIGO: Kidney Disease Improving Global Outcomes.

^d^SMASK: Smartphone Medication Adherence Saves Kidneys.

^e^Weekly SMASK reports and from clinic visits for all subjects.

^f^TSRQ: Treatment Self-Regulation Questionnaire.

^g^GCOS: General Causality Orientations Scale.

^h^HCCQ: Health Care Communication Questionnaire.

^i^eGFR: estimated glomerular filtration rate.

^j^GFR: glomerular filtration rate.

^k^TSUQ: Telemedicine Satisfaction and Usefulness Questionnaire.

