### Clinic Resting Blood Pressure

BP evaluations will be conducted at enrollment; randomization; and 1, 3, 6, and 12 months. Patients will be seated upright with right arm resting on a table at heart level and a proper cuff size will be fitted. A Dinamap Pro-Care 200 BP device (GE Healthcare, Buckinghamshire, United Kingdom) will be used to take the clinic BP measurements. The Dinamap has been validated following standard auscultatory methods from the British Hypertension Society and the Association for Advancement of Medical Instrumentation [66]. The Dinamap, as well as all other BP devices used in the trial, are calibrated according to the manufacturers’ specifications. A reading will be taken immediately, after 5 minutes of rest, and following a 2-minute interval. The average of the last two readings will be used in the analyses. Subjects in the SMASK group will use the same protocol (ie, a series of 3 BP readings with 5 and 2 minutes in between the first and second readings and between the second and third readings, respectively) at home for BP self-monitoring. This functionality will be embedded within the SMASK app and automatically guide the participants through the protocol with audio guides, timer count downs, and chimes when each waiting period is complete.

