#### Exploratory Outcomes Measures

In exploratory analyses, change in eGFR, variability of calcineurin trough levels, and 24-hour ambulatory BP will be compared between the two groups using pooled *t* tests (or nonparametric tests, as appropriate). If the end-of study outcomes for eGFR and 24-hour BP are missing, they will be imputed using multiple imputation methods. Further, frequency distributions of adverse events and serious adverse events will be determined, and proportions for the SMASK versus SC groups will be compared using Chi-square analyses.

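### The between-arm test of adverse event proportions is open to differential detection, because only SMASK patients have home BP, alerts and weekly physician reports

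*Protocol article*

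**What the plan says.** Under Statistical Analyses, Exploratory Outcomes Measures, the protocol article states that "frequency distributions of adverse events and serious adverse events will be determined, and proportions for the SMASK versus SC groups will be compared"; the test named is chi-square. That sentence gives no source of events, observation window or restriction to common visits.

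The arms are observed as follows:

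- **SMASK only** (Prototype section): "They will be instructed to measure their BP in the morning and evening every third day by using our resting BP protocol". Research staff are emailed and the participant is contacted "when they fail to measure BP or when the measured BP is outside of the threshold ranges established by the treating physician". The treating physician receives a weekly summary. Under Mobile Health Intervention, this arm "will receive the SMASK mHealth system, described in detail above, for the 6-month active trial".
- **SC** (Attention Control Standard Care Group): clinic visits as needed, a round-the-clock coordinator phone line, the medication tray with reminders off, and health-tip messages.
- **Both arms** (Clinic Resting Blood Pressure): "BP evaluations will be conducted at enrollment; randomization; and 1, 3, 6, and 12 months". Under its adverse events heading, Table 1 lists the "Medication Side Effects Scale" at every evaluation point, without distinction by arm.

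Under Blinding, outcome assessors are blinded for primary and secondary outcomes; adverse events are in neither group. The physician managing SMASK patients does not know which patients are enrolled as SC.

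**The concern.** A comparison of event proportions reads as a comparison of harm only if an event has a similar chance of being recorded in each arm. Here one arm has extra channels through which a low or high BP, or a complaint raised during a contact, could come to notice. The blinding arrangement points the same way: the managing physician can recognise an event in a SMASK patient as a trial event, but not in an SC patient whose enrolment is unknown to that physician.

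The intervention aims at lower BP and more timely medication changes. BP-related events are therefore a natural safety question, and they are the class most exposed to unequal detection. An excess in SMASK could be partly detection and be read as harm, a true excess could be dismissed as detection, and a true reduction could be masked. The results are meant to prepare a multisite trial.

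**Working it through.** The article gives no figure for adverse event ascertainment or for BP occasions per arm, so there is nothing to reproduce. Two calculations frame the point.

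**1. Scheduled BP occasions in the active phase**

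Inputs: two home sessions every third day (Prototype section); 6 months, taken as 180 to 183 days; three shared study visits, at 1, 3 and 6 months (Clinic Resting Blood Pressure).

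- Home sessions = (days / 3) × 2: 180/3 × 2 = 120; 183/3 × 2 = 122.
- Against three study visits: 120/3 = 40.0; 122/3 = 40.7.
- Adding SMASK's own visits: (120 + 3)/3 = 41.0; (122 + 3)/3 = 41.7.

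The ratio depends on what is counted:

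| Counting rule | Ratio |
|---|---|
| All 12 months, 4 visits per arm: (120 + 4)/4 | 31 |
| Randomization visit also counted: (120 + 5)/5 | 25 |
| 6 clinic readings per arm (assumed): (120 + 6)/6 | 21 |
| 9 clinic readings per arm (assumed): (120 + 9)/9 | 14.3 |
| Single readings over 182 days, with k ambulatory readings at 6 months (k = 24 to 72 assumed): (364 + 9 + k)/(9 + k) | 12 to 5.5 |

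In the last row, 364 = 182/3 × 2 × 3 readings per session, and 9 = 3 visits × 3 readings. Every version shows a clear imbalance in BP measurement. None is a ratio of adverse event ascertainment.

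**2. What incomplete detection in SC would do to the test**

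Assumptions: 40 per arm; two-sided 0.05; the same true risk p in both arms; SMASK records every event; SC records a share d of them. The shares d and risks p are not in the document.

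With p1 = p, p2 = d × p, difference D = p1 − p2 and mean m = (p1 + p2)/2:

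- se0 = √[m(1 − m) × 2/40]
- se1 = √[(p1(1 − p1) + p2(1 − p2))/40]
- P(significant) = Φ((D − 1.96 se0)/se1) + Φ((−D − 1.96 se0)/se1)

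Example with p = 0.30, d = 0.75: p2 = 0.225, D = 0.075, m = 0.2625, se0 = 0.0984, se1 = 0.0980. The two terms are Φ(−1.20) and Φ(−2.73), or 0.115 + 0.003 = 0.118.

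| True risk | d = 0.90 | d = 0.75 | d = 0.50 |
|---|---|---|---|
| 10% | 0.05 | 0.07 | 0.14 |
| 30% | 0.06 | 0.12 | 0.36 |
| 50% | 0.07 | 0.20 | 0.64 |

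Mild under-detection in SC hardly matters. Detection of half to three quarters, with events that are not rare, takes the error rate well above 5%.

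**The case against.** The strongest reply is that the link from surveillance to recorded events is not in the document. No section says that a home reading, an alert or an alert contact is logged as an adverse event. Staff are emailed and participants are contacted, but the text does not say that staff make the contact or ask about symptoms. The one instrument named for adverse events is the side-effects scale, given at the same visits in both arms. Definitions and collection forms may sit in a fuller protocol that is not shown, and the comparison is exploratory, in 80 patients, with no decision rule.

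Much of this stands. It is why the size of the bias cannot be stated and why silence on collection forms is not the complaint. It does not remove the point. The article commits to a chi-square test of adverse and serious adverse event proportions regardless of how events were found. A self-report side-effects scale cannot supply the serious events, so the test must draw on other sources, and the documented asymmetry can reach those.

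A reader might go further and infer that the test measures detection rather than harm, or that no safety conclusion is possible. The documents do not support that. The 40:1 ratio counts scheduled BP sessions, many events are not found with a BP cuff, and SC also has routine visits, the phone line and ambulatory BP at 6 months. Nor can a ratio of sessions be turned into event rates. With an assumed 0.25% chance per independent session, one gets 1 − 0.9975^124.3 = 26.7% against 1 − 0.9975^3 = 0.75%, but both the rate and the independence are invented.

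**Conclusion.** The point holds in limited form. The planned comparison of adverse event proportions is open to differential detection in favour of more recorded events in SMASK, mainly for BP-related and other non-serious events. Serious events are probably less affected.

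The documented facts are the unequal surveillance and a test that takes no account of it. The magnitude is not documented. Over the illustrated range (true risk 10% to 50%, SC detecting 50% to 90% of what SMASK detects), the chance of a spurious significant result runs from about 5% to 64%, and where the trial lies in that range is unknown. The conclusion assumes that at least some events reach the record through SMASK-only channels, which the article neither states nor excludes. It is worth correcting because this is the article's stated between-arm comparison of adverse events and the change is cheap.

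**What to change.** In Exploratory Outcomes Measures, base the between-arm comparison on events ascertained the same way in both arms: the side-effects scale and clinic BP at 1, 3, 6 and 12 months, and serious adverse events over the same dates. Scheduled ascertainment is then 4 occasions against 4.

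Beside it, report all adverse and serious adverse events by arm, flagging those first detected through home BP, alerts or SMASK reports. State in advance that an excess confined to flagged events will not be read as evidence for or against harm. The full table is needed because simply dropping flagged events could hide harms caused by the intervention itself.

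The cost is a few sentences, a source-of-detection flag and some extra tabulation. Home BP already goes to the study server, and the Table 1 fidelity checklists cover BP uploads and phone alerts, which should help assign the source although enrolment is complete. The drawbacks are fewer events in the test and some remaining inequality where an alert prompts a clinic contact.

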### Qualitative Studies

After the conclusion of the 6-month active trial evaluation, each member of the SMASK group will be approached to participate in a key informant interview of “lived experiences” during the trial. Topic areas with probes will cover expectations, experiences, adherence, motivation, and advice from family and friends. The SMASK lead physician, the transplant nurse coordinator, and other involved staff will be invited to participate in individual interviews to assess the SMASK program from the providers’ point of view. Topics of assessment will include attitudes, barriers and facilitators for use, fidelity, and impact on therapeutic inertia. We will use the constant comparative method of qualitative analysis to code the interviews’ transcript data using NVivo 10.0. Transcripts will be independently reviewed and coded by two reviewers. Once no new themes emerge, thematic saturation will have been reached. We will compare/contrast themes from participants and providers. We will synthesize and integrate the multiple quantitative and qualitative data sources using a triangulation approach. These collective findings will guide further refinements in the SMASK system prior to our efforts to acquire external funding to enable a multisite effectiveness RCT.

## Results

The SMASK project received funding from NIDDK in June 2016, obtained institutional review board approval in April 2016, and began data collection in July 2016. As of July 2018, we have completed enrollment with a total sample size of 80 participants. Currently, we are analyzing baseline data and upon completion of analysis of the final participant in the 6-month active trial, we will begin analyzing preliminary data to be submitted for peer-review publication.

Approval for important protocol modifications will be sought from the institutional review board. Written informed consent was obtained from all patients before enrollment by a trained research coordinator. There are no anticipated risks associated with participation in the study. Patients are free to withdraw at any time. Data will be kept confidential and anonymized for analyses.

## Discussion

Despite evidence that medication nonadherence is a major contributor to suboptimal outcomes in kidney transplantation, little progress has been made toward improving medication adherence. To date, research aimed at improving medication adherence in this patient population has been hampered by the use of convenience samples, indirect measures of medication adherence, and ineffective strategies. We aim to address some of these shortcomings in this trial. mHealth technology offers an opportunity to unobtrusively monitor patients, to react in real time to indicators of patient nonadherence, and to tailor the intervention to foster likelihood of sustained adherence to the regimen. Our previous research suggests that the use of an mHealth intervention in this patient population is promising.

This study is novel in both in its design and implementation. To our knowledge, this is the first RCT involving kidney transplant recipients that aimed to evaluate the efficacy of an mHealth medical regimen self-management system (SMASK), which was developed using an iterative design process guided by synergistic tenants from behavioral and technology application theories and direct guidance from kidney transplant recipients, transplant physicians, and associated health care team members. Importantly, the SMASK program utilizes timely regimen reminder tactics with immediate feedback of the results to the patient and real-time relay of patients’ regimen engagement to a HIPPA-compliant server. This allows for the use of automated, patient-tailored, motivational, and social reinforcement messages framed upon their degree of adherence. Importantly, the health care provider is intimately involved via weekly tailored emailed subject summary reports that allow more timely medical management decisions aimed at improved medication adherence, earlier BP control, and avoidance of unnecessary escalation of care. Collectively, these strategies are directed at enhancing patients’ self-efficacy to perform the medical regimen behaviors and improving the levels of autonomous, self-directed motivation to sustain these behaviors across time with the ultimate aim of improving long-term graft survival.

There are several limitations to this study that need to be addressed. First, although the study recruits from a single transplant center, limiting its generalizability, the center is the sole transplant provider for the state of South Carolina and has a catchment population of over 4.6 million persons that encompass a wide range of ethnic, educational, and socioeconomic backgrounds. Second, while it cannot be assumed that the subjects’ willingness to use the SMASK system can be divorced entirely from the appeal of the financial compensation, we targeted the compensation at a level that would only cover the inconvenience and cost of otherwise unnecessary travel and time spent waiting. Finally, while the current study duration of only 12 months is long enough to demonstrate improvements in medication adherence and BP control, it will not be long enough to demonstrate significant improvements in graft function or graft survival. However, these outcomes will be the focus of subsequent longitudinal studies, and participants in this study will be asked to continue providing relevant data to assess longer-term outcomes.

In conclusion, this study will provide important and novel data regarding the efficacy of the mHealth SMASK system to improve medication adherence and BP control in a medication-nonadherent cohort of uncontrolled hypertensive kidney transplant recipients. An efficacious SMASK intervention would lead to a larger, multicenter, effectiveness RCT powered to evaluate clinical events in a real-world setting and with the potential to demonstrate improved outcomes at lower cost than the standard of care.

## Appendix

Multimedia Appendix 1 National Institutes of Health (NIH) peer-review reports.

## Abbreviations

CNI: calcineurin inhibitor
cv: coefficient of variation
eGFR: estimated glomerular filtration rate
ESRD: end-stage renal disease
HIPAA: Health Insurance Portability and Accountability Act
ITT: intent to treat
KDIGO: Kidney Disease Improving Global Outcomes
mHealth: mobile health
MUSC: Medical University of South Carolina
NIDDK: National Institute of Diabetes and Digestive and Kidney Diseases
SBP: systolic blood pressure
SC: standard care
SMASK: Smartphone Medication Adherence Saves Kidneys
